### Endpoint Definitions and Hypothesis

The primary endpoint of the study will be a device oriented complex endpoint (DOCE). A complex endpoint has been defined, to assess hemostasis devices from both important clinical viewpoints: its efficacy in containing puncture site bleeding and its safety in terms of preserving radial artery patency and integrity.

DOCE will encompass the following: post-operative bleeding with visible hematoma formation after hemostasis device removal classified using the EASY methodology (17) (I), RAD, encompassing vessel dissection, (pseudo)aneurism and/or fistula formation (II) and RAO (III). These three parameters will be measured and quantified first at 24 hours after hemostasis device removal or at hospital discharge (whichever comes sooner), and again assessed at the 60-day follow-up visit.

Secondary endpoints will focus on human resource requirements and economics of devices. These include initial compression to achieve primary hemostasis (I), overall compression device usage time (II), and number of compression devices needed (III). Primary hemostasis is defined as the time in minutes, from application of the hemostasis device to the first successful decrease of the initial torniquet pressure, with success indicating no repeat bleeding from the puncture site. Overall compression time refers to total time of devices used as a hemostasis tool. In cases of acute bleeding following device use, a new, freshly opened tool may sometimes be required if the first one failed to contain bleeding. According to the RAPHE protocol, in case of initial device failure, a second, identical tool is to be utilized. If the second device also fails to contain puncture site bleeding, a bail-out hemostatic device will be employed. Thus, our last tertiary endpoint has been defined as follows: the need for a bailout compression method (I).

We hypothesize, that utilizing either of the novel bioactive devices in a standalone arrangement will prove clinically non-inferior to the other study and the control MCD, respectively. Furthermore, we assume, that the use of either one of the standalone bioactive devices will require less compression time, fewer human resources, and less management to successfully handle as compared to the MCD.

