### Patient Data Collection

Collection of patient and procedure data will be performed using a web based electronic case report platform (eCRF).

Demographics that the RAPHE study will be gathering include age, gender, height, weight, and BMI. The accumulated patient history will focus on relevant cardiovascular and other diseases that are known or are assumed to influence hemostasis parameters and thus bleeding of study patients. Collected data will consist of presence of hypertension, presence of dyslipidemia, smoking habits, presence and type (insulin or non-insulin dependent) of diabetes mellitus, prior acute coronary events, prior PCI, prior surgical revascularization, prior stroke, presence of malignancy, presence of liver disease, left ventricular ejection fraction, glomerular filtration rate and thrombocyte count.

Data surrounding the radial puncture itself will also be collected in detail. Overall procedure time, radial artery diameter, any prior punctures, presence of calcium in the radial artery via sonographic evaluation, size of the largest applied introducer sheaths are all recorded.

All relevant times in conjunction with hemostasis device use are detailed and documented. Initial compression of potassium-ferrate and chitosan devices and initial air amount of the pneumatic MCD will be noted, along with the time needed to achieve primary hemostasis. Total time of hemostasis devices will be precisely measured up to the minute in accuracy.

Concomitant medication especially those, influencing puncture site bleeding episodes will all be precisely collected for later assessment. All parenteral and oral anti-coagulant and anti-platelet medication types and utilized doses will also be logged.

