### Randomization Procedure

Randomization of consented subjects may only take place in the absence of exclusion criteria after removal of the last coronary catheter, by a physician participating in the study. It will take place in a 1:1:1 ratio, independently for every site via a computer algorithm, between the: pneumatic balloon MCD, potassium-ferrate disc and 100% chitosan sponge devices.

The pneumatic balloon based MCD serving as the control device will be placed on the introducer sheath inflated with the provided syringe to 12 ml-s with simultaneous removal of the introducer. An additional 2 ml-s of air will be inflated in case of acute bleeding and repeated if needed. It will be removed via a simplified patent hemostasis protocol (24), in which, after achieving primary hemostasis, exact titration to true PH we will be achieved by removing 2–3 ml-s of air every 10–15 min using a pulse oximeter to verify patency. At 0 ml-s of remaining air the device will be removed. These procedures will be carried out by qualified nursing staff. Nurses have been instructed to strictly adhere to the PH protocols and to contact study physicians in case of any potential adverse events, especially those in conjunction with radial hemostasis.

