The standalone potassium ferrate disc and chitosan sponge devices will both be used in a similar way. They will be placed onto the junction of the intact skin and introducer and manually compressed. To aid better initial compression and prevent device adhesion to bloody surgical gloves, a ball gauze will be placed on the chitosan device. The potassium-ferrate disc will be compressed alone. During compression the introducer will be removed, allowing for a visible amount of blood to appear, which will activate the hemostatic properties in both devices. Strong manual compression will be held for 1 min. Devices will then be banded and held in place using self-adherent wraps as detailed above. Strong, occlusive fixation of the devices will be upheld for a total of 10 min, after which the self-adherent bond will be fully unwrapped until the hemostasis device is visible. By this time both devices will have activated and initiated the coagulation cascade and are firmly attached to the puncture site. If acute bleeding occurs, an additional, minimum 5 minutes of compression will be applied. If initial devices are no longer fit for use, a new similar one will be used. Re-wrapping will then occur without the application of relevant pressure, in a non-occlusive way. During this time the wrapping will only protect the hemostasis device from external influence (e.g., accidental dislodgement, slipping etc.). If the second randomized study device also fails to contain puncture site bleeding a bail-out device of choice shall be applied as per protocol, the choice of which is left to the discretion of the attending physician. After a period of 120 ± 15 min the self-adherent wrapping will be removed. The chitosan sponge device will also be removed using sterile saline irrigation. The potassium-ferrate disc will remain in place and removed by the patient after 24 hours post-procedure.

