RAPHE will focus on RAO, RAD and bleeding equally, from a device-oriented endpoint as all present clinical challenges influence quality of life of patients. With RAO, a conduit for further use is eliminated and clinical signs of upper extremity ischemia may present, necessitating surgical or endovascular treatments. Damage to the radial artery, clinically mostly manifesting as (pseudo)aneurysm and fistula formation can cause substantial pain/discomfort, paresthesia and even a palpable mass above the site of the puncture often causing a thrill in case of an arterio-venous fistula. These pathologies will likely require interventional methods or surgical repair to avoid chronic vascular conditions (5–8) and may cause a notable decrease in quality of life if left unchecked and/or untreated. Bleeding as the most common complication after TRA if serious may present as a significant or even critical issue. Thus a “perfect” compression device has a DOCE of zero per cent, as it causes no bleeding, RAO or RAD. In the RAPHE study we expect an overall DOCE rate, encompassing everything above of around 15% in all three arms of the trial.

The main goal of the study will be to determine, how standalone bioactive chitosan and/or potassium ferrate devices fare against the gold standard pneumatic airbladder based MCD. Besides clinically relevant safety and efficacy profiles, we will opt to also explore if fewer human resources are required to manage said bioactive devices. As per the RAPHE protocol, bioactive devices only require one adjustment, shortly after application and may require less overall compression time. Reducing the need for extensive human resource PH management and continuous MCD adjustments in high-volume centers is favorable, due to a multitude of factors. As bioactive devices do not require adjustments every 10–20 min, additional staff, managing strict PH protocols may be allocated elsewhere. In the RAPHE study we assume that patients randomized into one of the two investigational arms (potassium ferrate disc or chitosan sponge) will achieve primary hemostasis quicker and require less overall compression time as compared to MCD control subjects. From an economic point of view, the RAPHE trial will also be assessing the need of hemostasis units per patient in all three arms, and record if bail-out compression devices are needed. We have no convincing assumptions regarding these endpoints, due to a lack of prior reported data or in-house registries.

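### Secondary endpoint II counts total device-use time but serves a hypothesis about compression time; in the chitosan arm about 85–92% of the counted time is without relevant pressure

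*Protocol article*

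**What the plan says.** All references are to the protocol article.

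- **Hypothesis.** Endpoint Definitions and Hypothesis assumes that "the use of either one of the standalone bioactive devices will require less compression time, fewer human resources, and less management" than the pneumatic compression device (MCD). The Discussion repeats this with the endpoint's own term: bioactive patients will "require less overall compression time as compared to MCD control subjects".
- **Endpoint.** The second secondary endpoint is listed as "overall compression device usage time (II") and defined so: "Overall compression time refers to total time of devices used as a hemostasis tool". Patient Data Collection matches that definition: "Total time of hemostasis devices will be precisely measured up to the minute in accuracy".
- **Bioactive arms.** Randomization Procedure gives 1 min of strong manual compression and 10 min of occlusive fixation, with at least 5 min more if bleeding occurs. After that, "Re-wrapping will then occur without the application of relevant pressure, in a non-occlusive way", and "During this time the wrapping will only protect the hemostasis device from external influence". The wrap and the chitosan sponge come off at 120 ± 15 min. The potassium-ferrate disc stays on, and the patient removes it after 24 hours.
- **Control arm.** The MCD is inflated to 12 ml, with 2 ml top-ups for acute bleeding. After primary hemostasis it is deflated by "removing 2–3 ml-s of air every 10–15 min using a pulse oximeter to verify patency", and it is removed at 0 ml.

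**The concern.** The hypothesis is about compression. The endpoint, by its name, its definition and its data item, is about device use. In the MCD arm the two nearly coincide, because the device is taken off when the bladder is empty. In the bioactive arms they separate after roughly 11 min, because the rest of the wear time is by the article's own description free of relevant pressure.

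One label therefore measures different things in different arms, and the planned superiority comparison does not answer the stated question. The counted time in the chitosan arm is also set mainly by a scheduled removal window, so it says little about how the device performs. At stake is the trial's conclusion on compression time, which is one of its stated reasons for preferring the bioactive devices. The primary endpoint is not affected.

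**Working it through.** The article gives no expected value for this endpoint, so there is no planned figure to reproduce. The check is arithmetic on the schedules in Randomization Procedure.

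**1. Time under pressure, bioactive arms.** 1 + 10 = 11 min; with the minimum extension for bleeding, 11 + 5 = 16 min. The extension has no upper limit. If the manual minute lies inside the 10 min, these become 10 and 15 min.

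**2. Pressure-free time counted for chitosan.** Wrap removal is at 120 ± 15, that is 105 to 135 min. The start of that clock is not stated; application is assumed.
- Lowest: 105 − 16 = 89 min, and 89/105 = 85%.
- Highest: 135 − 11 = 124 min, and 124/135 = 92%.
- With the manual minute inside the 10 min, the highest is 135 − 10 = 125 min (93%).
- If the clock starts at the re-wrap, the pressure-free time is the whole 105–135 min.

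**3. Pressure-free time counted for the disc.** If use runs to removal at 24 h (1440 min): 1440 − 16 = 1424 to 1440 − 10 = 1430 min. The article does not say when the disc's clock stops.

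**4. MCD time.** Let T be the time to first deflation, which is not stated. Steps from 12 ml: 12/3 = 4 to 12/2 = 6. The first step occurs at T, so the remaining steps add (steps − 1) × interval: 3 × 10 = 30 min to 5 × 15 = 75 min. Total MCD time = T + 30 to 75 min. If T is one interval (10–15 min), the total is 40–90 min. From 14 ml after one top-up there are 5 to 7 steps, and the tail is 4 × 10 = 40 to 6 × 15 = 90 min.

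**5. When the direction reverses.** The MCD equals a 120 min wrap when T = 120 − 75 = 45 to 120 − 30 = 90 min. For a 105 min wrap the break-even T is 30–75 min; for 135 min it is 60–105 min. A smaller T makes chitosan longer by device-use time; a larger T makes it shorter.

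**6. MCD times that the Introduction cites from other studies**, against a 120 min wrap and 11 min under pressure:

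| MCD time (min) | Chitosan − MCD, device use | Chitosan − MCD, under pressure |
|---|---|---|
| 50 | 120 − 50 = +70 (reversed) | 11 − 50 = −39 |
| 120 | 120 − 120 = 0 (tie) | 11 − 120 = −109 |
| 160 | 120 − 160 = −40 (as hypothesised) | 11 − 160 = −149 |

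The gap between the last two columns is 120 − 11 = 109 min in every row. The shift does not depend on the MCD time; only the sign does.

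**7. Scale.** Assuming an SD of 43 min (the cited 160 ± 43 min) and 200 × 0.9 = 180 patients per arm, the standard error of a difference is 43 × √(2/180) = 4.5 min. The shift is many times that.

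**The case against.** The other side has several fair points.

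- **The sign is not known.** A reader might infer that the definition reverses the hypothesised result, and that a superiority test will be highly significant under either definition. The article supports neither. T is a measured outcome with no stated expectation, top-ups lengthen MCD time, and the three cited MCD times give reversal, a tie and no reversal. A near tie would not be highly significant. This stands: reversal is possible, not established.
- **Device-use time is a legitimate measure.** The secondary endpoints are said to address human resources and economics, and usage time suits that purpose. This stands as a reason to keep it, under its own name. It does not make it a test of compression.
- **The definition may exclude the protective phase.** Serving as a tool for hemostasis could be read that way. The endpoint's listed name and the recorded total device time point to the other reading. If both are open, the tested quantity is not fixed, and the two readings differ by about 90–125 min.
- **Start and stop rules belong in the full protocol or SAP.** Fine timing rules do. Here, however, the article states a definition, and that definition does not fit its own hypothesis and procedure.
- **Secondary endpoint I already captures the pressure phase.** Largely so: in an uncomplicated bioactive patient, the first successful pressure decrease is the unwrapping at about 10–11 min. But endpoint I stops at the first decrease in the MCD arm too, so it does not compare total compression.
- **Time under pressure has its own bias.** It counts MCD minutes titrated to patent flow, while uncomplicated bioactive time is fixed by the schedule. This stands and limits how the result may be worded.

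**Conclusion.** The concern holds as a mismatch between hypothesis and endpoint. As defined, endpoint II adds about 89–125 pressure-free minutes to each chitosan patient and essentially none to an MCD patient, at any MCD duration. This rests on counting device use up to removal and on a clock that starts at application; a clock that starts at the re-wrap makes it 105–135 min. Reversal of the hypothesised direction is conditional: against a 120 min wrap it occurs only if the MCD comes off sooner than that, and T, which decides this, is not given. The 90–125 min is a wrap figure and describes the chitosan arm. For the disc the excess is about 1424–1430 min if use is counted to removal at 24 h, and the direction is then reversed at all three cited MCD times. Because this is one secondary endpoint, the point is a correction that should be made and not a threat to the trial's main result.

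**What to change.** In Endpoint Definitions and Hypothesis, split secondary endpoint II.

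- **(a) Time under applied pressure.** Bioactive arms: manual compression, occlusive fixation, any repeat compression, and the pressure time of a second or bail-out device, ending at the non-occlusive re-wrap. MCD arm: from inflation to 0 ml. Use (a) for the hypothesis of less compression time.
- **(b) Device dwell time.** Report it separately under that name, with its start and stop stated for each device, including when the disc's clock stops.

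Align the wording of Patient Data Collection and the Discussion with this split. Confirm that the eCRF records the re-wrap time; the article says that all relevant device times are documented but does not name this one.

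The cost is endpoint wording and possibly one eCRF field. Patient care does not change. The downside should be stated in the plan: uncomplicated bioactive time in (a) is largely fixed by the schedule and overlaps with endpoint I, and MCD time in (a) includes the titration to patent flow. The result should therefore be presented as a difference between hemostasis protocols, not as evidence of device performance.

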### Sonographic Evaluation and Follow-up

Examinations will be conducted three times during the trial, by a certified physician or licensed sonography specialist, blinded to all study procedures. The protocol will include a color and pulse-wave Doppler assessment and two-dimensional imaging in a longitudinal and transverse plane to assess arterial occlusion and/or damage, i.e., dissection, (pseudo)aneurism, and fistula formation.

The initial, pre-screening examination will be carried out prior to any puncture, to assess artery parameters and dimensions, accounting also for any potential intrinsic abnormalities of the region. The second sonographic evaluation of the puncture site will take place 24 hours after the procedure or at patient hospital discharge, whichever occurs first. All the above sonographic parameters will be collected, along with an Allen-test to account for palmar arch integrity along with radial artery bleeding and hematoma formation, which will be assessed using the EASY study classification. EASY class I and II will be considered minor, while III and above major bleeding events. Furthermore, all relevant clinical adverse events will also be collected and evaluated.

The third and final radial sonography and Allen-test will be conducted at 60 days follow-up, with a ± 10-day window. This time window was chosen as per empiric knowledge of the sites involved and also the fact that a previous trial (The RadPress trial—unpublished) with similar PH methods did not see any rational to further delay the follow-up visit to a later timepoint. Similarly, as with the first follow-up, all potential adverse events will be collected, and sonographic and clinical parameters of the radial puncture site examined.

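### The protocol gives conflicting times for the first primary-endpoint assessment and for disc removal, so bleeding after removal goes largely unexamined in the potassium-ferrate arm

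*Protocol article*

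**What the plan says.** Three sections of the protocol article bear on the first assessment after the procedure.

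- **Endpoint Definitions and Hypothesis.** The bleeding component is "post-operative bleeding with visible hematoma formation after hemostasis device removal", graded on the EASY scale. All three components (bleeding, radial artery damage, radial artery occlusion) are read "first at 24 hours after hemostasis device removal or at hospital discharge (whichever comes sooner", and again at 60 days.
- **Sonographic Evaluation and Follow-up.** The same visit, including the EASY grading, is timed from the procedure: "The second sonographic evaluation of the puncture site will take place 24 hours after the procedure or at patient hospital discharge, whichever occurs first". The last visit is at 60 ± 10 days. Scans are done "by a certified physician or licensed sonography specialist, blinded to all study procedures".
- **Randomization Procedure.** For the two bioactive arms: "After a period of 120 ± 15 min the self-adherent wrapping will be removed". For chitosan: "The chitosan sponge device will also be removed using sterile saline irrigation". For the disc: "The potassium-ferrate disc will remain in place and removed by the patient after 24 hours post-procedure". For the pneumatic control: "At 0 ml-s of remaining air the device will be removed".

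**The concern.** The endpoint section makes device removal the event after which bleeding counts. The follow-up section places the first examination no later than 24 hours after the procedure, and the device section places disc removal later than that. The three statements cannot all be followed in the ferrate arm.

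The conflict falls on one randomised arm. Chitosan and pneumatic-device patients are normally examined some hours after their device has come off. A ferrate patient managed to schedule is examined before that period begins. If removal provokes bleeding, it happens after the visit, in the patient's own hands. The next planned examination is about two months later.

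The primary hypothesis is non-inferiority, and under-counting events in an experimental arm makes that easier to show. Bleeding that nobody examined or recorded at the time cannot be recovered in the analysis. The disc on the wrist also bears on the stated blinding of the examiner, in a trial that is otherwise open-label.

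**Working it through.** **Step 1: timeline by arm, from the protocol's own figures.**

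| Arm | Device off | First visit (follow-up section) | Device at first visit |
|---|---|---|---|
| Pneumatic | about 40–90 min after primary haemostasis | 24 h or discharge, whichever is first | normally off |
| Chitosan | with the wrap, 105–135 min | same | normally off |
| Ferrate disc | later than 24 h, by the patient | same | normally on, wrap already removed |

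The pneumatic figure starts from 12 ml, with 2–3 ml released every 10–15 min. The fastest course is 12/3 = 4 steps × 10 min = 40 min, and the slowest is 12/2 = 6 steps × 15 min = 90 min, if no air is added.

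**Step 2: does the endpoint section's clock remove the problem?** Only in part. A ferrate patient discharged before taking the disc off is still examined with it on, because discharge comes sooner. One who stays 24 h beyond removal is examined more than 24 + 24 = 48 h after the procedure, against about 2 + 24 = 26 h for chitosan. The two clocks therefore give different visits, and neither gives the arms the same observation window.

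**Step 3: the sample size, to fix the margin used below.** With 15% in both arms, one-sided 5% and 80% power:

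n = (1.645 + 0.842)² × (2 × 0.15 × 0.85) / 0.10² ≈ 158 per arm.

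This matches the stated 158, so the calculation used an absolute margin of 10 points. The Sample Size Calculation section calls the margin relative. A relative 10% would be 1.5 points and would need 7007 per arm. The timing conflict does not affect this figure.

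**Step 4: illustration of what an under-count would do.** Let b be the number of percentage points of DOCE missed in the ferrate arm only. The documents do not give b; 1 to 3 points is an assumption. For scale, the Discussion expects haematoma in 5–7% and DOCE in about 15%. Take 200 per arm, control 15%, and a true ferrate rate at the margin (25%), so the observed ferrate rate is p = 0.25 − b. Non-inferiority is declared if the one-sided 95% upper bound of the difference lies below 10 points:

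P(declare) = Φ[(0.10 − (p − 0.15)) / SE − 1.645], with SE = √[(0.15 × 0.85 + p(1 − p)) / 200].

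| b (points) | p | SE | P(false non-inferiority) |
|---|---|---|---|
| 0 | 0.25 | 0.0397 | 5.0% |
| 1 | 0.24 | 0.0394 | 8.2% |
| 2 | 0.23 | 0.0390 | 12.9% |
| 3 | 0.22 | 0.0387 | 19.2% |

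**Step 5: blinding.** The wrap is off at about 2 h, so at the first visit the disc lies uncovered on the site to be scanned. Its presence points to the ferrate arm, and its absence points to one of the other two. The article describes no masking.

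**The case against.** The strongest reply is that little is actually hidden.

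- **Bleeding before removal is still gradable.** Occlusive fixation of the disc ends at 10 min and re-wrapping is without relevant pressure. By a 24-hour visit the puncture has normally been free of occlusive pressure for most of a day. A haematoma spreading beyond the disc would be seen and graded. This stands. A reader might infer that bleeding cannot be detected at all in the ferrate arm; the documents do not support that. What escapes visit 1 is bleeding at or after self-removal.
- **There is later capture.** Adverse events and the state of the puncture site are reviewed at day 60, and occlusion and damage are re-scanned then. This also stands, so the gap concerns part of one component. But a day-60 review is not equivalent to the post-removal EASY grading that the other arms receive at the first visit, and more than 80% of haematomas are expected to be EASY I–II.
- **Not every ferrate patient is affected.** Bail-out cases, dislodged discs and, on the endpoint section's clock, late discharges are exceptions. The claim is limited to patients managed to schedule.
- **The size is not in the documents.** A reader might take half of the 5–7% haematomas as missed and put the bias near 3 points. Nothing in the protocol supports that share. A missed haematoma also removes no DOCE event if the patient has occlusion or damage as well. The expected component rates sum to 13–20% (5–7, 5–8 and 3–5) against a composite of about 15%, so overlap is possible. The illustration further uses a confidence-bound rule, whereas the Statistical Analyses section names Fisher's exact test.
- **Unblinding is an inference.** How the site is presented to the examiner may be settled in the full protocol. A reader might also infer that blinding fails in the ferrate arm alone; that is not right, because an absent disc is informative too.

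None of this removes the conflict between the three sections.

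**Conclusion.** The concern holds as a conflict over the timing of a primary-endpoint assessment, with a likely consequence in one arm. As written, ferrate patients managed to schedule have essentially no examined post-removal period at the first visit, while chitosan and pneumatic-device patients do. The likely direction is under-counting of the bleeding component in the ferrate arm, which favours non-inferiority.

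The size is unknown. The rise in false non-inferiority from 5% to about 8–19% is an illustration. It rests on an assumed under-count of 1 to 3 points, 200 per arm, a true rate exactly at the margin, a one-sided 5% confidence-bound rule, and the absolute margin that reproduces 158. It should not be quoted as an estimate of bias in this trial.

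The statement that the examiner is blinded is doubtful at the first visit for all arms. The 60-day scan is not affected, since no device is then worn.

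The sections need to be reconciled, because events not observed at the time cannot be restored later.

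**What to change.** Reconcile the endpoint, device and follow-up sections. How long the disc is worn is for the investigators to settle; the points below concern measurement only.

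1. Time the first visit from one clock, sheath removal, in all three arms.
2. Define the DOCE bleeding component as any EASY-graded haematoma from sheath removal to one cut-off that is common to all arms and lies after device removal in each of them.
3. Record bleeding after the first visit with the same patient-report item in the eCRF in all three arms. Using it for the disc arm alone would create a new difference in ascertainment.
4. State that the first-visit reading may be unblinded.
5. Report the 60-day occlusion and damage comparison as a supportive analysis. It should not be a further success criterion, since it leaves out bleeding and any early occlusion that has resolved.

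The cost is a protocol clarification, one eCRF item for every patient, some contact with patients already discharged when the common cut-off is reached, and one supportive analysis. The main drawback is that patient-reported bleeding is less precise than an examination.
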